## Abstract

**Background:**

The stress that results from preterm birth, requisite acute care and prolonged physical separation in the Neonatal Intensive Care Unit (NICU) can have adverse physiological/psychological effects on both the infant and the mother. In particular, the experience compromises the establishment and maintenance of optimal mother-infant relationship, the subsequent development of the infant, and the mother's emotional well-being. These findings highlight the importance of investigating early interventions that are designed to overcome or reduce the effects of these environmental insults and challenges.

**Methods:**

This study is a randomized controlled trial (RCT) with blinded assessment comparing Standard Care (SC) with a novel Family Nurture Intervention (FNI). FNI targets preterm infants born 26-34 weeks postmenstrual age (PMA) and their mothers in the NICU. The intervention incorporates elements of mother-infant interventions with known efficacy and organizes them under a new theoretical context referred to collectively as calming activities. This intervention is facilitated by specially trained Nurture Specialists in three ways: 1) In the isolette through calming interactions between mother and infant via odor exchange, firm sustained touch and vocal soothing, and eye contact; 2) Outside the isolette during holding and feeding via the *Calming Cycle*; and 3) through family sessions designed to engage help and support the mother. In concert with infant neurobehavioral and physiological assessments from birth through 24 months corrected age (CA), maternal assessments are made using standard tools including anxiety, depression, attachment, support systems, temperament as well as physiological stress parameters. Quality of mother-infant interaction is also assessed. Our projected enrolment is 260 families (130 per group).

**Discussion:**

The FNI is designed to increase biologically important activities and behaviors that enhance maternally-mediated sensory experiences of preterm infants, as well as infant-mediated sensory experiences of the mother. Consequently, we are enlarging the testing of preterm infant neurodevelopment beyond that of previous research to include outcomes related to mother-infant interactions and mother-infant co-regulation. Our primary objective is to determine whether repeated engagement of the mother and her infant in the intervention's calming activities will improve the infant's developmental trajectory with respect to multiple outcomes. Our secondary objective is to assess the effectiveness of FNI in the physiological and psychological co-regulation of the mother and infant. We include aspects of neurodevelopment that have not been comprehensively measured in previous NICU interventions.

**Trial Registration:**

ClinicalTrials.gov: NCT01439269

## Background

The overall goal of our program of research is to test the hypothesis that increasing the amount of specific types of mother-infant and family-calming interactions will improve neurodevelopmental and emotional outcomes in preterm infants, and behavioral and emotional outcomes in mothers.

The stress that results from preterm birth, and the requisite acute care and prolonged physical separation in the NICU, can have adverse physiological/psychological effects on both the infant and the mother [1-4]. In particular, the experience compromises the establishment and maintenance of an optimal mother-infant relationship [4-6]. These findings highlight the importance of investigating early interventions that are designed to overcome or reduce the effects of these environmental insults and challenges.

There have been numerous trials of interventions for mothers of preterm infants. However, several aspects make this current study different. Few studies have examined the effectiveness of biologically-relevant mother-infant calming activities in their breadth and complexity using an RCT design. With the exception perhaps of some Kangaroo Care (KC) or Kangaroo Mother Care (KMC) interventions, very few trials incorporate strategies that relate to mother-infant interactions while the infant is in the NICU, even fewer while the infant is confined to the isolette. No such trial to our knowledge has specifically identified the "Calming Cycle" (see Methods and Design below) as the central focus of the intervention, or included an extended family support component for the mother and infant. Few trials have included as extensive an array of physiological and psychological mother and infant outcome measures. Finally, few trials have followed the patients for two years. We seek to address these deficiencies by carrying out an RCT of a family-based nurture intervention (FNI) among the families of pre-term infants born 26-34 weeks PMA into the NICU, using blinded assessments of effectiveness with long-term follow-up.

By nurturing interactions and activities, we mean those mother-infant interactions inherently involved in mothering such as holding, touching and communicating. These activities engage the sensory systems of both the mother and her infant (i.e., sight, hearing, smell, touch, taste, temperature, vestibular, kinesthetic) [7,8]. An emerging body of preclinical and clinical evidence is revealing the critical importance of specific mother-infant interactions in regulating the physiology and behavior of the infant [9,10], and for shaping the development of their behavior and physiology [11-15]. Our intervention is designed to enlist these proximal mechanisms for the improvement of developmental outcome in premature infants.

Nurturing interactions are equally important for establishing and maintaining the mother's physiological and behavioral adaptations necessary for the care of her infant [16,17]. Based on the literature and on the extensive clinical experience of the first author, early introduction of repeated mother-infant sensory calming interactions is expected to alleviate maternal depression, anxiety, and guilt, as well as lessen infant aversion to contact that stems from separation/isolation and stressful medical procedures. These sensory calming interactions are expected to have physiological and behavioral effects on both infant and mother, including increasing the mother's feeling of competence. Once the physiology of mother and infant are altered, we hypothesize that these changes will be sustained over time.

We are combining elements of prior interventions with known efficacy and testing these within the theoretic context we call the mother-infant *Calming Cycle*. This cycle, which is depicted schematically in Figure 1, was described by the first author in the 1980's. It was subsequently refined and published as a therapeutic intervention suitable for mothers and children with a wide range of ages and disorders [18-21]. In FNI, the *Calming Cycle *procedure has been adapted for mothers with preterm infants. In so doing, we are enlarging the testing of preterm infant neurodevelopment beyond that of previous research to include outcomes related to mother-infant interactions and mother-infant co-regulation. Our outcome measures, especially those that measure mother-infant co-regulation, include aspects of neurodevelopment that have not been extensively used in a NICU intervention and never in the integrated way we propose (i.e., mother-infant physiological measures during the *Calming Cycle*).

**Figure 1 F1:**
[figure not shown]
**Conceptual representation of Calming Cycle hypothesis**. During a *Calming Cycle *mothers and infants cycle through: 1) separate mother and infant discomfort/distress, 2) mutually shared distress, 3) mutual resolution of discomfort/distress, 4) mutual calm that may include periods of eye-to-eye contact and/or infant sleep. Over time *Calming Cycle *interactions will lead to more rapid reductions and lower absolute levels of discomfort and distress in both the mother and the infant. (Note: The break in the separation line indicates that in the NICU mother-infant separation times vary widely in the NICU).

Our intervention focuses on enabling mothers to engage in certain mother-infant interactions as early as possible after birth, within the constraints of the NICU environment. These interactions begin with odor-cloth exchange, firm sustained touch and vocal soothing, and eye contact while the infant is confined to the isolette; skin-to-skin contact and *Calming Cycle *activities are added to these as soon as the infant is able to be held and fed by the mother. The intervention also provides other family members with strategies to support the mother as she continues these interactions with her infant within the NICU and at home.

The intervention used in this trial is based on a rich history of ethological and experimental studies in animals and humans, as well as from the 30-year clinical experience of the first author treating developmental disorders. Our approach also draws on existing early intervention literature, including studies on the effectiveness of kangaroo care (KC) [22-24], Creating Opportunities for Parent Empowerment (COPE) [25,26], and Family Centered Care (FCC) [27,28].

The rationale underlying many of the features of this intervention is also supported by a recent meta-analysis of early NICU interventions involving parents [29]. The findings of this systematic review show the importance of early intervention and teaching parents skills and/or involving parents in the care of the preterm for enhancing child development. The meta-analysis focused on one primary outcome, broad neurodevelopment, which is one of the primary infant outcome measures of our trial. The prior findings support several key features of FNI: early intervention is critical, greater amounts of intervention are more effective, targeting both mother and infant is important, increasing certain types of physical contact is efficacious, and family support and involvement is of benefit.

The present report describes in detail the FNI methodology and summarizes the measures used to evaluate the efficacy, safety and practicability of this intervention. These assessments include a broad spectrum of infant physiological, infant behavioral and family health outcomes, starting from the time of enrollment in the NICU through the first two years of the infant's life. Our primary objective is to determine the effectiveness of FNI in improving the neurodevelopmental and emotional outcomes in preterm infants. Our secondary objective is to assess the ability of FNI to improve co-regulation in the mother and her preterm infant.

## Methods and Design

FNI is a randomized controlled trial designed to determine the short- and long-term physiological and behavioral effects of a family nurture intervention on preterm infant development. The intervention takes place over the course of the NICU stay. FNI is designed to help the mother and her preterm infant engage in interactive biologically important activities and behaviors that enhance the maternally-mediated sensory experiences of preterm infants, as well as the infant-mediated sensory experiences of the mother. Extended family members are also engaged and encouraged to adopt both a supportive and supplementary role in the process. Our primary hypotheses are that the FNI group will have increased infant brain activity as assessed by electroencephalogram (EEG) power and better basic neurobehavioral function close to term and at 18 months CA as compared to the Standard Care (SC; described below) group. Our secondary hypotheses are that the FNI group will have decreased stress responses in mother and infant at four months CA, fewer maternal anxiety and depressive symptoms after discharge from the NICU, as well as better maternal attachment and support systems as compared with the SC group. In addition to the aforementioned measures, we are also collecting samples of infant blood, breastmilk and stool samples from mother and infant.

### Ethical considerations

Written informed consent is obtained from families prior to enrolment in the trial. This trial and all protocols within it have been approved by the Institutional Review Board of Columbia University Medical Center, where the trial is being conducted.

### Participants

The study setting is a high acuity neonatal intensive care unit at Morgan Stanley Children's Hospital in New York, NY. The intervention is conducted during the infant's stay in the NICU. All follow-up assessments are conducted at adjacent facilities to the hospital at Columbia University Medical Center.

Families are eligible for recruitment if the infant is born a singleton or twin in the hospital between 26 and 34 weeks post-menstrual age (PMA), if the mother has no history of drug addiction or psychosis or other severe mental illness, if the mother understands and speaks English, and if there is at least one adult other than the mother in the home. Infants are excluded from the study if their birth weight is below the third percentile for gestational age or if there are significant congenital defects. Families are excluded if there is not at least one adult other than the mother in the home, since in such cases the critical family support component of the intervention could not be completed or evaluated (see Family Support Sessions below).

Recruitment is undertaken by a trained research assistant (RA). The RA reviews birth records daily. After obtaining permission from the attending physicians of both mother and infant, the RA invites qualifying families in the Obstetrics Ward or NICU to participate in the study. The RA describes the study procedures to the parents, including the randomization process, and obtains a written consent form from those enrolling. Mothers wishing to think about the study or talk it over with family members are encouraged to make a decision within 24 hours so that the intervention can start as early as possible.

Mothers complete initial assessments after consent and families are then assigned to the FNI intervention group or the SC group using a randomized block design. For randomization, six group assignment cards (3 FNI: 3 SC) are placed in envelopes and sealed. The envelopes are shuffled, numbered and placed in a packet prior to use. The RA withdraws an envelope from the packet to determine group assignment. Within 1 to 2 days of consenting, mothers assigned to the FNI group meet with a Nurture Specialist (NS) designated to facilitate the intervention and begin to carry this out, as described in the Intervention Methods section below. Mothers of infants assigned to the SC condition receive NICU standard care as described in the Standard Care section below. Twins are "clustered" for purposes of randomization, with both infants being assigned to the same group along with the mother.

To determine the total sample size necessary to ensure statistical power of not less than 0.8 to detect differences between group means, we considered the detectable difference for each of the primary outcome variables that would be of interest for a successful study result. Our experience and that of others suggested that effect sizes within the 'medium' range would be achievable (i.e., 0.4 to 0.6). Therefore, given the two independent samples created within the RCT design, assuming a significance level of α = .05 for a two-tailed test, we estimate that we will have at least 80% power (1-*β *≥ .80) to detect a difference between groups for effect sizes and total sample sizes as described in Table 1. Experience with the pilot study suggests that we could expect attrition at a rate as high as 40%. To accommodate this, we intend to recruit a total of N = 260 participants from which a final sample size sufficient to detect all differences of interest should be achieved.

**Table 1 T1:** Power analysis

Outcome Measure	PMA	Reference Population *μ *(*σ*)	Detectable Difference |*μ*_FN_-*μ*_SC_|	Effect Size *d*	Total N Required

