##### Objective assessments

Neurobehavioral assessments, including the NNNS and Bayley-III Scale, are conducted by clinical psychologists blinded to group assignment. Infant and mother physiological data (e.g., cardio-respiratory, EEG) is collected by non-blinded research assistants but coding, data reduction and preliminary data analysis is done without knowledge of group assignment. Only final group comparison analyses are, of necessity, performed with knowledge of group status.

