To reduce the bias potentially associated with a randomized controlled trial of this size in a modern NICU, the following criteria developed by the Cochrane Collaboration for evaluation of intervention studies [87] will be adopted: (1) the sequence generation of allocating subjects will be random; (2) group designation will be concealed until after consent is obtained and the first set of questionnaires is administered; (3) the blinding of participants, research and clinical staff, and outcome assessments will be achieved to the extent possible; 4) outcome data will be complete; (5) outcome reporting will not be selective.

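### Fixed packets of six envelopes, drawn by the research assistant role that also recruits, let late assignments in each block be inferred and so weaken the promised concealment

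*Protocol article*

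**What the plan says.** In Methods and Design, Participants, families are assigned "using a randomized block design". The mechanism is then given. A block is made up by hand: "six group assignment cards (3 FNI: 3 SC) are placed in envelopes and sealed". On how that set is made ready, the article adds: "The envelopes are shuffled, numbered and placed in a packet prior to use". On who takes the next step, it states: "The RA withdraws an envelope from the packet to determine group assignment". Twins go to the same arm, so the family is the unit drawn.

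The same section gives the RA role the steps before the draw. The RA checks birth records each day and, once both attending physicians agree, "the RA invites qualifying families in the Obstetrics Ward or NICU to participate in the study". The RA also explains the randomization and obtains consent. Mothers may take about a day to decide, and they complete initial assessments between consent and assignment.

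Under Potential limitations the article adopts a bias criterion that "group designation will be concealed until after consent is obtained" and the first questionnaires are done. The described procedure contains no variation in block size.

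**The concern.** Sealed, shuffled and numbered envelopes hide each card. They do not hide the composition of a block whose size and 3:3 split are fixed, because the person drawing sees each arm as it comes out. Once three cards of one arm have been used, the rest of the packet is known. Here the role that learns those results also invites the next family.

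The stake is selection at entry. The Family Nurture Intervention section asks FNI mothers to commit to at least four one-hour sessions a week, and standard-care mothers have no such commitment. A recruiter who can guess the next arm could, without intending to, time or word an approach according to a mother's availability or an infant's stability. Potential limitations names both as factors that matter and expects availability not to differ by group, an expectation that depends on concealment. Blinded NNNS and Bayley-III assessment cannot undo selection at entry. The significance tests in Planned analyses are described for family socio-demographic characteristics, so they would not be expected to show selection on availability or motivation.

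**Working it through.** The article gives no figure for predictability, so there is none to reproduce.

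**Inputs.** Block of 6 with 3 cards per arm (Participants); 260 families, 130 per group (Abstract, Methods).

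**Step 1: chance that the rest of the packet is known after k draws.** This needs all three cards of one arm to be out.

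- k = 0, 1 or 2: impossible, 0.
- k = 3: 2 × C(3,3) × C(3,0) / C(6,3) = 2/20 = 10%.
- k = 4: 2 × C(3,3) × C(3,1) / C(6,4) = 6/15 = 40%.
- k = 5: 2 × C(3,3) × C(3,2) / C(6,5) = 6/6 = 100%.

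**Step 2: share determined at the draw, all earlier draws known.** Position i follows i − 1 draws.

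| Position | 1 | 2 | 3 | 4 | 5 | 6 |
|---|---|---|---|---|---|---|
| Certain in advance | 0 | 0 | 0 | 10% | 40% | 100% |

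Expected number per block = 0.1 + 0.4 + 1.0 = 1.5. Share = 1.5/6 = 25%. Over 260 families, 0.25 × 260 = 65 (the 43 complete blocks give 43 × 1.5 = 64.5). Enumerating all 20 orders agrees: 60% of blocks have exactly one determined assignment, 30% have two and 10% have three, and 0.6 × 1 + 0.3 × 2 + 0.1 × 3 = 1.5.

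**Step 3: what is known when a family is approached.** If no earlier family is waiting for its draw, knowledge at approach equals knowledge at the draw, and Step 2 applies. If some are waiting, fewer results are visible. The number waiting is an assumption, because the article gives no accrual rate.

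- One waiting: position 5 sees 3 draws (10%) and position 6 sees 4 (40%). (0.1 + 0.4)/6 = 8.3%, about 22 of 260.
- Two waiting: only position 6 can be determined, having seen 3 draws (10%). 0.1/6 = 1.7%, about 4 of 260.

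**Step 4: guessing short of certainty.** Someone who knows all earlier draws and always guesses the arm with more cards left is right, by position, with probability 0.5, 0.6, 0.6, 0.7, 0.7 and 1.0. The sum is 4.1, and 4.1/6 = 68.3%, against 50% under full concealment.

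**Step 5: effect of changing the blocks** (illustrative sizes, not from the article; all earlier draws known). A fixed block of 8 leaves 20% determined, and a fixed block of 10 leaves 16.7%. Blocks drawn at random from 4, 6 and 8 leave about 2% determined in a simulation of 200 trials of 260. In that simulation the observer knows the possible sizes but not which size is in use.

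**The case against.** The strongest reply is that the procedure is sound in most respects. Cards are sealed, shuffled and numbered, and opened only after consent and the first assessments. Recruitment also follows stated criteria: birth records are reviewed daily, two physicians must agree, qualifying families are invited, and the aim is to start early. Nothing describes an RA choosing among eligible families or delaying an approach. That stands. The check shows that some assignments can be inferred, not that anyone acted on them, and the 68.3% measures guessability, not bias in an outcome.

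Four stronger readings are tempting, and the article does not support them.

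- *A quarter of assignments are known before the family is approached.* This needs every earlier draw to be known and no other family pending. The invitation, the decision time, consent and baseline assessments all fall between approach and draw, so overlap is possible. Nor does the article say that one RA makes all draws or that RAs share results.
- *Nobody independent of recruitment holds the sequence.* The article does not say who prepared or kept the packets. The full protocol may, and silence in a journal article is not evidence of absence.
- *Drawing an envelope, and not expressly the next in number, is a separate flaw.* Numbering suggests use in order, and an unopened shuffled card is no more predictable when taken out of order.
- *The RAs are declared unblinded.* Objective assessments says physiological data "is collected by non-blinded research assistants", which concerns data collectors, not recruiters. The point does not need it, because whoever draws an envelope learns the arm.

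It is also the plain reading, but not an explicit statement, that each packet holds exactly one set of six. Mixing several sets in one packet would lower the predictability.

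**Conclusion.** The point holds as a weakness in a stated rule. A fixed 3:3 block of six, drawn by the role that screens, invites and consents, allows the end of each block to be inferred. The concealment commitment under Potential limitations is therefore weakened. It does not fail outright, since each card stays hidden until opened.

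The size is at most 25% of assignments, about 65 of 260. This assumes one set of six per packet, full knowledge of earlier draws in that packet and no family pending. It falls to about 8% with one family pending and below 2% with two, and it is also lower if several RAs do not share results. The document does not allow the true value within that range to be fixed, and no bias in any outcome has been shown. The change is worth making because it is cheap and selection at entry cannot be repaired later.

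**What to change.** For the families still to be enrolled, have someone not involved in recruitment prepare permuted blocks of randomly varying size (for example 4, 6 and 8) and keep the sizes from the RA. Supply them as one continuous numbered series, not as packets that reveal where a block ends. Open envelopes strictly in order, each only after consent and the questionnaires due before assignment (E1 in Table 2) are logged. The variation in size does most of the work: an independent custodian of fixed blocks of six would not stop an RA who learns each arm from counting.

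Release through the Data Coordinating Center is an alternative if it has the capacity. Confidentiality of Study Data describes that centre only as overseeing data management and storage, so the capacity is an assumption. If an independent holder or in-order opening is already in place, the sponsor should say so.

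The cost is a short amendment and a small amount of preparation. The largest possible arm imbalance inside an unfinished block rises from 3 (half of 6) to 4 (half of 8). Outcomes, visits and sample size are unaffected.

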##### Twins

Twins as well as singletons are included in the study because twinning occurs commonly in the hospital where this study is being conducted, due largely to increased use of *in vitro fertilization *[51]. Twins will be "clustered" and not separated in the randomization process, since FNI cannot be delivered to only one twin. The challenges of nurturing twins in the context of the study protocol are discussed during sessions with family members and an individualized plan is developed and agreed upon. When possible, mothers will hold both twins at once. Alternatively, the father and mother will take turns holding the twins at the same time. Two follow-up assessments will be impacted; only one twin per family (the first born) will be assessed at the 4- and 12-month follow-up visits, since it was determined that the first mother-twin interaction will compromise the novelty of the second mother-twin interaction and the time required to film two twins in one day will be prohibitive. The treatment of twins in the data analysis will be based upon recognition that within the twin pair the intervention cannot be independently applied.

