### Planned analyses

Descriptive statistics will be derived for all predictor and outcome variables. Family socio-demographic characteristics are not expected to differ by study group, but significance tests will be conducted to confirm the success of the randomization process. Outcomes for the two study groups including infant EEG measures, stress and development, and maternal stress and depression will be compared at each measurement interval (intake, term, 4, 12, 18, and 24 months CA) using independent t-tests for differences between means for continuous data and chi-squared tests for differences between proportions for categorical data. The Bonferroni correction will be applied to account for multiple testing. Longitudinal analyses assessing differences over time will be conducted using repeated measures ANOVA for continuous data and Kruskal-Wallace or Friedman's adaptation of this test for non-parametric data. Generalized linear models will be used to assess the variability in infant development, as measured by Bayley-III Scales at 18 months CA. This variability is explained by repeated maternal and infant psychological and neurological factors after controlling for baseline family socio-demographic characteristics.

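### Infant outcomes are compared by unadjusted t-tests across 26–34 weeks and twin status: valid, but adjusting for both would gain precision at almost no cost

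*Protocol article*

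**What the plan says.** **Population.** The Participants section of the protocol article admits infants "born a singleton or twin in the hospital between 26 and 34 weeks post-menstrual age".

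**Allocation.** The same section says "families are then assigned to the FNI intervention group or the SC group using a randomized block design". The mechanics are that "six group assignment cards (3 FNI: 3 SC) are placed in envelopes and sealed" and "The envelopes are shuffled, numbered and placed in a packet prior to use". Twins go to the same arm as each other and their mother. No stratum is named, and no separate packets for gestational age or twin status.

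**Analysis.** Planned analyses compares the arms at each measurement interval "using independent t-tests for differences between means for continuous data", and by chi-squared tests for proportions, with a Bonferroni correction. No covariates are attached to these comparisons. A generalized linear model is planned for 18-month Bayley-III; the baseline characteristics it controls for are family socio-demographics. The baseline balance tests concern the same characteristics. The Twins section says the analysis will recognise that "within the twin pair the intervention cannot be independently applied". That addresses dependence within a pair, not balance between arms.

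**Limitations.** Potential limitations accepts that differences in infant health may affect outcomes independently of the intervention, but states no adjustment.

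**The concern.** Gestational age at birth and twin status are known before an envelope is drawn. Both plausibly relate to infant outcome, and the population is deliberately wide on the first and mixed on the second. The allocation as described balances neither, and the main tests use neither.

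Two things are at stake. Variance explained by gestational age stays in the error term, which costs power. And if the realised allocation happens to be unbalanced, the stated comparisons do nothing about it. Power has little slack on some outcomes: after the 40% attrition that the article allows for, 156 of 260 remain, against Table 1 requirements of 150 (EEG), 154 (HRV) and 174 (Bayley-III).

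**Working it through.** **Inputs from the protocol article.** Two-sided α = .05; power .80; N = 260; attrition up to 40%; Table 1 differences and SDs: EEG 0.2 and .434, Bayley-III 6.0 and 14. Analysed sample: 260 × 0.6 = 156, or 78 per arm.

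**Assumed, because the article gives no figure.** Correlation r between gestational age and outcome .3 to .5, with lower values shown; SD of gestational age 2.0 to 2.6 weeks. The power figures treat infants as independent.

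**Step 1: the plan's own figures.** For a two-sample t-test, d = difference/SD.
- EEG: 0.2/.434 = .461, total N = 150, as in Table 1.
- Bayley-III: 6/14 = .429, total N = 174, as in Table 1. (The printed d of .41 would need 188–190; that is a separate matter, and 6/14 is used here.)

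**Step 2: is the unadjusted test valid?** In 20,000 simulated null trials with permuted blocks of six, no strata and N = 258, the unadjusted t-test rejected in .051, .048 and .049 of trials when gestational age explained 0, 10% and 30% of outcome variance. So it is valid.

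**Step 3: power from adjustment.** Adjusting for a covariate with correlation r shrinks the residual SD by √(1 − r²), so the effective d becomes d/√(1 − r²). With 78 per arm:

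| r | EEG d | EEG power | Bayley-III d | Bayley-III power |
|---|---|---|---|---|
| 0 | .461 | .816 | .429 | .758 |
| .1 | .463 | .820 | .431 | .762 |
| .2 | .470 | .831 | .437 | .775 |
| .3 | .483 | .850 | .449 | .796 |
| .4 | .503 | .877 | .468 | .827 |
| .5 | .532 | .910 | .495 | .867 |

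In equivalent sample size, 156/(1 − r²) − 156 gives about 15, 30 and 52 infants at r = .3, .4 and .5.

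**Step 4: chance imbalance.** The SD of the difference in mean gestational age is SD × √(2/n).
- 78 per arm: 0.32, 0.37 and 0.42 week for SD 2.0, 2.3 and 2.6. A difference of 0.5 week or more has probability .12, .17 and .23.
- 130 per arm, as randomized: probability .04, .08 and .12.

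With SD 2.3 and 78 per arm, the unadjusted test's type I error splits as follows:

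| r | imbalance ≥ 0.5 week (17.5% of trials) | all other trials | overall |
|---|---|---|---|
| .3 | .075 | .045 | .050 |
| .4 | .095 | .041 | .050 |
| .5 | .119 | .035 | .050 |

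**The case against.** **The unadjusted test is not wrong.** A reader might infer that imbalance in gestational age or twin share biases the comparison, or that the false-positive rate is 8–12%. The article does not support this. Chance imbalance is already part of the standard error. The raised rates belong only to the unlucky draws and are offset by rates below .05 in the rest. This objection stands, so the point concerns efficiency only.

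**More mature infants and intervention dose.** A longer NICU stay may mean more intervention, but only within the intervention arm. That is variation in effect, not confounding between arms. This stands too.

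**The correlation is assumed.** NNNS is done at 36 and 40 weeks PMA, term EEG at 39–42 weeks, and Bayley-III at corrected age, so maturity at testing is largely standardised. Gestational age at birth may still predict outcome, but r = .5 could be generous. At r = .1 the EEG gain is only .004.

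**Not every outcome is tight.** NNNS needs 96 of the 156 available, with power about .95. With all 260 analysed, EEG power is already .959 unadjusted.

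**Silence in a condensed article.** A packet of six does not strictly exclude separate packets per stratum, and covariates could be set in an analysis plan that is not shown. The first leaves a single unstratified series as an inference. The second has less force, because the article does state its tests and the covariates of its one adjusted model, and neither factor is among them.

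**Stratified envelopes.** A reader might conclude that the allocation must be changed. Stratifying by twin status and a 30-week split makes four strata, some sparse with blocks of six. A two-level split also keeps only about 64–75% of r², so at r = .3 to .5 EEG power would reach about .84–.89. Continuous adjustment does better without touching the envelopes.

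**Conclusion.** The point holds as an improvement in efficiency and robustness, not as an error or contradiction. As written, the between-arm comparisons of infant outcomes ignore two baseline factors that are available before allocation, and the one adjusted model omits them.

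Under an assumed r of .3 to .5 and the full 40% attrition, adjustment takes EEG from .816 to .85–.91. It brings Bayley-III, which falls short at .758, to about .80–.87. The benefit shrinks with lower correlation or better retention and is slight for NNNS. No bias or inflation of overall type I error is shown.

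**What to change.** For the between-arm comparisons of continuous infant outcomes (term EEG, NNNS, HRV, Bayley-III), replace the independent t-test with a linear model of outcome on arm, gestational age at birth as a continuous covariate, and twin status. Cluster standard errors by family wherever both twins contribute; at 4 and 12 months only the first-born is assessed. Add both covariates to the generalized linear model for 18-month Bayley-III. Fix this before any comparison by arm.

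The cost is two model terms, using data already known at enrolment. Stratifying the remaining envelopes is optional; it would add packet series and some incomplete blocks, and the gain above does not depend on it.
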